## Abstract

**Background:**

Colorectal cancer is one of the major neoplasms and a leading cause of cancer death worldwide, and new preventive strategies are needed to lower the burden of this disease. Metformin, a biguanide, which is widely used for treating diabetes mellitus, has recently been suggestive to have a suppressive effect on tumorigenesis and cancer cell growth. In a previous study conducted in non-diabetic subjects, we showed that oral short-term low-dose metformin suppressed the development of colorectal aberrant crypt foci (ACF). ACF have been considered as a useful surrogate biomarker of CRC, although the biological significance of these lesions remains controversial. We devised a prospective randomized controlled trial to evaluate the chemopreventive effect of metformin against metachronous colorectal polyps and the safety of this drug in non-diabetic post-polypectomy patients.

**Methods/Design:**

This study is a multi-center, double-blind, placebo-controlled, randomized controlled trial to be conducted in non-diabetic patients with a recent history of undergoing colorectal polypectomy. All adult patients visiting the Yokohama City University hospital or affiliated hospitals for polypectomy shall be recruited for the study. Eligible patients will then be allocated randomly into either one of two groups: the metformin group and the placebo group. Patients in the metformin group shall receive oral metformin at 250 mg per day, and those in the placebo group shall receive an oral placebo tablet. At the end of 1 year of administration of metformin/placebo, colonoscopy will be performed to evaluate the polyp formation.

**Discussion:**

This is the first study proposed to explore the effect of metformin against colorectal polyp formation. Metformin activates AMPK, which inhibits the mammalian target of rapamycin (mTOR) pathway. The mTOR pathway plays an important role in the cellular protein translational machinery and cell proliferation. Patients with type 2 diabetes taking under treatment with metformin have been reported to be at a lower risk of cancer development than those not taking under treatment with metformin. We showed in a previous study that metformin suppressed the formation of human colorectal ACF. We therefore decided to conduct a study to determine whether metformin might suppress the formation of human colorectal polyps.

**Trial registration:**

This trial has been registered in the University hospital Medical Information Network (UMIN) Clinical Trials Registry as UMIN000006254

## Background

Colorectal cancer (CRC) is a major neoplasm worldwide [1], and both its prevalence and mortality have been increasing [2]. Removal of colorectal polyps has been to shown to reduce the risk of future development of colorectal cancer and advanced adenoma [3,4]. On the other hand, patients with polyps (adenomas and/or hyperplastic polyps) constitute a high-risk group for the development of metachronous colorectal polyps and/or CRC [5]. Therefore, a paradigm shift from surveillance for early detection of cancer or adenomas (polypectomy) to new strategies for prevention, including chemoprevention, is needed to lower the burden of this disease. Several large epidemiologic and/or clinical studies have evaluated the possible preventive effects of more than 200 agents, including fiber, calcium, and non-steroidal anti-inflammatory drugs (NSAIDs), including aspirin and selective cyclooxygenase-2 (COX-2) inhibitors, in protecting against CRC development [6]. NSAIDs, especially COX-2 inhibitors, administered either alone or in combination with other agents, have shown the most promise, until date, for CRC risk reduction [4], although reports have revealed an increased risk of serious cardiovascular events associated with the use of COX-2 inhibitors [7,8]. In light of the adverse cardiovascular effects of COX-2 inhibitors and lack of demonstrable efficacy of the other agents that had initially shown promise in this setting, novel drugs that would be both safe and effective for CRC prevention need to be developed. CRC is associated with lifestyle-related diseases, such as diabetes mellitus and obesity [9-12], therefore, we considered that these conditions might represent potential new targets for CRC chemoprevention.

Metformin (1,1-dimethylbiguanide hydrochloride) is a biguanide derivative that has long been used widely for treating diabetes mellitus [13]. It decreases basal glucose output by suppressing gluconeogenesis and glycogenolysis in the liver and increasing glucose uptake by the muscle. Because metformin does not directly stimulate insulin secretion, it is associated with a lower risk of hypoglycemia than other oral antidiabetic drugs [14]. The molecular mechanism involved in the action of metformin is liver kinase B-1dependent activation of AMP-activated protein kinase (AMPK) [15]. Patients with type 2 diabetes under treatment with metformin have been reported to be at a lower risk of cancer development (including CRC) than those not under treatment with metformin [16,17]. This evidence suggests that metformin might be a candidate agent for CRC chemoprevention in diabetic patients. However, since diabetes mellitus itself is a risk factor for cancer, treatment of diabetes mellitus may reduce the risk; therefore, it is still unclear whether the suppressive effect of metformin against CRC may be exerted by the direct chemopreventive effect of the drug or be mediated by its antidiabetic effect. Therefore, we considered that in order to validate the chemopreventive effect of metformin, a clinical trial in nondiabetic patients needs to be conducted.

In previous studies, we demonstrated the chemopreventive effect of metformin in two rodent models (a genetic model and a chemically-induced cancer model) and one human study of colorectal carcinogenesis. We showed that metformin suppressed the development of intestinal polyps in adenomatous polyposis coli (APC^Min/+^) mise, a murine model of familial adenomatous polyposis [18]; furthermore, we showed that metformin suppressed azoxymethane-induced formation of colorectal aberrant crypt foci (ACF) by activating AMPK [19]. Both studies were performed in nondiabetic mice, which suggested the direct chemopreventive potential of metformin per se. In the study conducted on nondiabetic human subjects, we showed that oral low-dose administration of metformin (250 mg per day) suppressed the formation of colorectal ACF and that the drug was safe [20]. ACF are considered as a reliable surrogate biomarker of CRC [21], although their biological significance still remains controversial. Therefore, in CRC chemoprevention trials, in general, the incidence of polyps or of the cancer itself is set as the study endpoint. Although the incidence rate of CRC would be the most reliable endpoint, use of this endpoint would be unsuitable for chemoprevention trials, because of the relatively low occurrence rate of CRC in the general population [22] and the long-term observation period that it would necessitate. Moreover, observation of polyps detected in annual colonoscopies until they grow into cancer would be fraught with ethical problems. Thus, we set the appearance of colorectal polyps as a suitable endpoint for our chemopreventive trial.

Thus, we devised a prospective randomized controlled trial to evaluate the chemopreventive effect of metformin against the development of metachronous colorectal polyps and the safety of this drug in nondiabetic post-polypectomy patients.

This is the first clinical trial of metformin as a chemopreventive agent against metachronous colorectal polyps in humans.

## Methods/Design

### Study design and setting

This study is designed as a multi-center, double-blind, placebo-control, randomized controlled trial to be performed in nondiabetic patients with a recent history of undergoing colorectal polypectomy. The study will take place at the Division of Gastroenterology, Yokohama City University Hospital, and its 5 affiliate hospitals. The coordinating office shall be at Yokohama City University Hospital, with the registration, randomized allocation and data collection to be conducted at this site.

### Ethical considerations and registration

The study protocol is in compliance with the Declaration of Helsinki [23] and the Ethics Guidelines for Clinical Research published by the Ministry of Health, Labour, and Welfare, Japan [24]. We obtained approval for this study from the Ethics committee of Yokohama City University Hospital on July 8^th ^2011. The protocol and informed consent forms were approved by the institutional ethics committee at each of the participating institutions. This trial has been registered in the University hospital Medical Information Network (UMIN) Clinical Trials Registry as UMIN000006254. Written informed consent for participation in the study will be obtained from all the participating patients. The trial results will be reported in conformity with the Consolidated Standards of Reporting Trials (CONSORT) 2010 guidelines [25].

### Eligibility criteria

All adult patients visiting the hospital for polypectomy will be recruited for the study.

The inclusion criteria are as follows:

1) No colorectal polyps present after the polypectomy

2) Age 40 to 80 years as on the date of informed consent

3) Willingness to provide written informed consent

The likelihood of development of colorectal polyps in the young is low and the diagnosis history of polyps in the young is usually related to familial adenomatous polyposis or hereditary non-polyposis colorectal cancer; on the other hand, the elderly have various complications. This was the rationale for our setting the age criterion for inclusion in this study as 40 to 80 years.

The exclusion criteria are as follows:

1) History of diabetes mellitus (use of medication and/or HbA1c over 6.5%)

2) History of regular use (defined as at least once per week) of NSAIDs and/or aspirin

3) History of bowel surgery

4) History of malignant disease (excluding carcinoma in adenoma, carcinoma in situ that has already been resected)

5) History of heart failure, renal failure, liver cirrhosis or chronic hepatic failure

6) History of familial adenomatous polyposis

7) History of hereditary non-polyposis colorectal cancer

8) History of inflammatory bowel disease

9) Pregnancy or possibility of pregnancy

10) Patients judged as inappropriate candidates for the trial by the investigators

### Intervention

All eligible patients will be allocated randomly to one of two groups, the metformin group and the placebo group. Endoscopists, doctors at the follow-up outpatient clinics and patients will be blinded to the allocation. Patients in the metformin group shall receive oral metformin at 250 mg per day, and those in the placebo group shall receive oral placebo tablet. At the end of 1 year of administration of metformin/placebo, colonoscopy will be performed to evaluate the polyp formation.

### Outcome measurements

The primary endpoint shall be the prevalence of colorectal polyps and number of polyps after 1-year's intervention. The endoscopic examinations and polypectomies will be performed using Olympus colonoscopes (model H260AZI). The day before the endoscopy, each patient will be instructed to consume a low-residue diet and shall receive 5 mg of oral sodium picosulfate. On the day of the endoscopy, the patients shall receive 2000 ml of polyethylene glycol (PEG). If the feces are not sufficiently clear, an additional 1000 - 2000 ml of PEG may be given to ensure sufficient bowel cleaning. At the time of the polypectomies, the endoscope shall be inserted into the cecum, and the entire colorectum will be carefully observed as the endoscope is pulled back. If any polyps are detected, polypectomy will be performed. At the end of 1 year of administration of metformin/placebo, the same endoscopists will perform the repeat endoscopic examinations. If a polyp(s) is detected at the repeat colonoscopy (after treatment for one year), a biopsy will be performed. A total of 6 endoscopists from Yokohama City University Hospital and the 5 affiliate hospitals will perform the polypectomies and endoscopic examinations. All procedures will be recorded on DVD, and all the polyps will be photographed. The number of polyps in each patient will first be counted by the operators during the performance of the colonoscopy. To further ensure validity, the number of polyps will be counted again through observation of the recorded DVD by 3 blinded expert endoscopists ([name], [name], and [name]). If these expert endoscopists judge the colonoscopic examination as having been inadequate in any case, that case will be excluded. The biopsied polyps will be evaluated by expert pathologists ([name] and [name]).

The secondary outcomes are (1) the drug safety; adverse events will be monitored by the doctor at every follow-up visit to the outpatient clinic. Adverse events will be graded according to the National Cancer Institute Common Toxicity Criteria for Adverse Events (NCI-CTCAE), version 4.0. Diarrhea, the most frequent adverse event related to use of metformin, will be watched for spontaneous resolution within a few days and/or managed by antiflatulent drugs. If Grade 3 or more severe adverse events appear, the follow-up doctor shall report it (them) to the coordinating office and the case will be withdrawn from the study at that point; (2) laboratory data (fasting blood glucose, fasting blood insulin, HbA1c, total cholesterol, LDL-cholesterol, blood urea nitrogen (BUN), creatinine); (3) the number of ACF. At the time of the 1-year colonoscopy and polypectomy, the lower rectal region from the middle Houston valve to the dentate line will be washed thoroughly with water, sprayed with 0.25% methylene blue, which would be left to stand for 2 min, then again washed thoroughly with water. The number of rectal ACF will be counted with a magnifying endoscope [21]; (4) physical examination findings (body weight, body mass index (BMI)). Metformin is widely used as an antidiabetic drug that improves insulin resistance. The effect of metformin on insulin resistance and the plasma lipid profile will be evaluated by comparing these parameters measured at the baseline and at 1 year in the metformin group and placebo group. All participants will receive physical examination and laboratory tests at the time of the 1-year endoscopic examination and polypectomy; (5) effects of metformin on the cell-proliferative and apoptotic activities in the rectal epithelium and polyps (if any). Colonic epithelial samples will be obtained from the same trial patients by biopsy at the time of the 1-year colonoscopy and polypectomy. The cell-proliferative activity will be evaluated by staining for the proliferative cell nuclear antigen (PCNA), and the cell-apoptotic activity by the terminal deoxynucleotidyl transferase-mediated dUTP-biotin nick end labeling (TUNEL) method; (6) expression levels of protein (AMPK, mTOR/S6K) in the rectal epithelium and polyps (if any) that are thought to be pharmacological targets of metformin. The expression levels of these proteins shall be determined by western blot analysis.

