### Sample size estimation

We previously showed that metformin administered at 250 mg/d for 1 month directly suppressed the formation of ACF. In that study, mean number of ACF per patient decreased significantly from 8.78 ± 6.45 (baseline) to 5.11 ± 4.99 (at 1 month, *p = 0.007*) [20]. Based on a similar study, Takayama et al. reported that sulindac administration at 300 mg/d for 2 months to post-polypectomy patients suppressed ACF formation, decreasing the number of ACF from 7.70 ± 4.04 (baseline) to 4.00 ± 2.95 (at 2 months, *p < 0.001*) [26]. From these reports, we estimated that metformin and sulindac may have equivalent effect on suppression of ACF formation. Moreover, from the same study, Takayama et al. reported that in the post-polypectmoy patients who received 2-months' intervention, the number of polyps (hyperplastic polyp and adenoma) at 1 year after the treatment was significantly lower in the sulindac group in comparison with that in the placebo group (26/48 (54.2%) vs. 15/48 (31.3%), *p = 0.025*) [26]. Therefore, we speculated that 1-year's treatment with metformin might yield equivalent suppression of metachronous polyp formation to that with sulindac. To detect the reduction in the number of metachronous polyps in the metformin group using the chi-square test with a two-sided significance level of 5% and a power of 80%, it was found that a sample size of 68 patients per group would be necessary. Assuming a 10% dropout rate, we propose to recruit 75 patients per group, that is, a total of 150 patients.

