### Statistical analysis

The prevalence of polyps in each group, the primary endpoint, will be compared between the metformin group and placebo group by the chi-square test. The safety, one of the secondary endpoints, will be similarly compared by the chi-square test. The remaining results in the two groups will be compared by the Mann-Whitney *U *test or Student's *t *test. A P value of < 0.05 shall be regarded as indicative of significance. The analysis will be performed using SPSS, version 17.0 (SPSS Inc., Chicago, Il.).

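### The primary endpoint is two outcomes in one section and one in another, and the sample size labels prevalence as number, so no decision rule applies when the two outcomes disagree

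*Protocol article*

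**What the plan says.** Three sections of the protocol article describe the efficacy outcome differently.

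- **Outcome measurements** names two outcomes: "The primary endpoint shall be the prevalence of colorectal polyps and number of polyps after 1-year's intervention". The six numbered secondary outcomes that follow do not include the number of polyps; the only count among them is of aberrant crypt foci.
- **Statistical analysis** names one: "The prevalence of polyps in each group, the primary endpoint, will be compared between the metformin group and placebo group by the chi-square test". Safety is also tested by chi-square. Everything else, which would include polyp number, falls under a general sentence, "The remaining results in the two groups will be compared by the Mann-Whitney" U test or Student's t test. A P value below 0.05 counts as significant throughout.
- **Sample size estimation** uses the word number. It introduces the sulindac study's result by saying that "the number of polyps (hyperplastic polyp and adenoma) at 1 year after the treatment was significantly lower in the sulindac group", but the figures given are 26 of 48 and 15 of 48 patients. The target is then worded as follows: "To detect the reduction in the number of metachronous polyps in the metformin group using the chi-square test". The outcome is that "a sample size of 68 patients per group would be necessary".

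No section says whether one or both outcomes must be significant, divides the 5% between them, or puts them in order.

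**The concern.** This is the trial's only efficacy decision, and the text supports more than one rule for making it. Suppose that prevalence is not significant and polyp number is. Under Outcome measurements a primary outcome has been met; under Statistical analysis the primary endpoint has failed. Either statement could be presented as prespecified.

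Two consequences depend on how the ambiguity is resolved. If either outcome may carry the claim, two tests at 5% do not keep the overall error at 5%. If both must succeed, power cannot exceed the power for prevalence alone. The count also has no planning basis: the article gives no mean or standard deviation for polyps per patient.

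An analysis plan can add detail to a protocol, but here two protocol sentences conflict, and the protocol itself has to say which one stands.

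**Working it through.** **1. Which outcome was sized?** Inputs from Sample size estimation: p1 = 26/48 = 0.5417, p2 = 15/48 = 0.3125, two-sided 5%, 80% power, equal groups.

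Unpooled two-proportion formula: n = (1.960 + 0.842)² × [p1(1−p1) + p2(1−p2)] / (p1−p2)²

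- p1(1−p1) + p2(1−p2) = 0.2483 + 0.2148 = 0.4631
- (p1−p2)² = 0.2292² = 0.0525
- n = 7.849 × 0.4631 / 0.0525 = 69.2, so 70 per group
- With the rates rounded to 54% and 31%: 7.849 × 0.4623 / 0.0529 = 68.6

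The stated 68 is reproduced within two patients. (The version with pooled variance under the null gives 72, and power of 77.7% at 68.) The calculation is therefore for the proportion of patients with a polyp, whatever the sentence calls it.

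**2. False-positive rate if either outcome counts.** Two independent tests at 5% would give 1 − 0.95² = 9.75%. Prevalence and count come from the same patients, and the test statistics for chi-square and Mann-Whitney correlated at 0.91 to 0.97 in simulation, so the real figure for that pair is lower. The article gives no count distribution, so Poisson and negative binomial counts (dispersion k) were assumed. No drug effect was assumed, with 68 per group and 40,000 trials per setting. Prevalence was either the control rate (54.2%) or about the average of the two planning rates (41/96 = 43%).

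| Prevalence, counts | Chi-square alone | Chi-square or Mann-Whitney | Chi-square or t | Any of the three |
|---|---|---|---|---|
| 43%, Poisson | 4.8% | 6.0% | 7.1% | 7.2% |
| 43%, k = 1 | 4.9% | 6.3% | 7.8% | 8.2% |
| 43%, k = 0.5 | 4.6% | 6.0% | 7.6% | 8.1% |
| 54.2%, Poisson | 4.6% | 6.4% | 7.3% | 7.6% |
| 54.2%, k = 1 | 4.9% | 6.9% | 8.2% | 8.8% |
| 54.2%, k = 0.5 | 4.7% | 6.7% | 8.4% | 9.2% |

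**3. Power if both must succeed.** With the planning rates, and counts that fall along with prevalence, power for both chi-square and Mann-Whitney was about 76-78%, against 77-78% for prevalence alone. The loss is small in this setting. It could be larger if the drug acted differently on the two outcomes.

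**4. Cost of keeping both as alternatives.** With alpha split to 0.025 each, prevalence alone needs, in the pooled form, n = [2.241 × √0.4894 + 0.842 × √0.4631]² / 0.0525 = 88 per group (72 at alpha 0.05), or 88/0.9 = 98 with 10% dropout. At 68 per group its power would be 68.2%. Polyp number could not be sized at all from the article.

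**5. The rules side by side.**

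| Rule | Supported by | Error rate | Consequence |
|---|---|---|---|
| Prevalence alone | Statistical analysis; the sample size arithmetic | 5% | Stated size applies |
| Either outcome | Possible under Outcome measurements | About 6-9% | Needs an alpha split or order |
| Both outcomes | Possible under Outcome measurements | Not above 5% | Power at most that of prevalence |

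**The case against.** The strongest reply is that the intended rule is easy to see. The section that fixes the test speaks of a single primary endpoint and one chi-square test, and the sample size is a two-proportion calculation that comes out at about 68. Those two sections agree in operation, and Outcome measurements is the outlier. Much of this stands: the word number in the sample size text is a wrong label, not a third competing definition, and the arithmetic favours prevalence. It does not remove the conflict, because the outcome definition itself still names two outcomes and the count is not placed among the secondaries.

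A reader might go further, in four ways that the document does not support:

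- **That the trial has two unadjusted routes to a positive claim.** This needs Outcome measurements to govern and either outcome to suffice. No section says that either suffices.
- **That the error rate has a ceiling of 9.75%.** That is the value for two independent tests. It is not a bound: two tests at 5% can reach 10% under some forms of dependence, and the figure does not apply to three tests.
- **That leaving Mann-Whitney or t open is a defect in itself.** The sentence covers all remaining outcomes, and assigning a test to each is commonly left to an analysis plan. It matters here only if the count is primary, and nothing says that the choice would be made after seeing the data.
- **That the sample size is wrong.** It is reproduced for prevalence; only its wording is at fault.

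**Conclusion.** The concern holds as an internal contradiction: two primary outcomes in one section, one in another, and a sample size sentence that names the count but sizes prevalence. The decision rule is undefined whenever the two outcomes disagree.

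The size of the harm is conditional. If either outcome counts, the false-positive rate rises from a nominal 5% to about 6-7% with chi-square or Mann-Whitney, and to about 7-9% if the t test may also be chosen. These ranges rest on assumed Poisson or negative binomial counts and null prevalences of 43% to 54%. If prevalence alone is primary, or both outcomes must succeed, there is no inflation. The figures are modest; the correction is needed because the trial's one efficacy conclusion depends on which sentence is read.

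**What to change.** - **Outcome measurements and Statistical analysis:** state one primary endpoint, prevalence, defined as the patient having at least one polyp at the 1-year colonoscopy.
- **Sample size estimation:** describe both the sulindac result and the target effect as the proportion of patients with at least one polyp.
- **Number of polyps:** list it as a named secondary outcome, tested only if prevalence is significant, with one prespecified method.

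A both-must-succeed rule or an alpha split would also settle the conflict. The first leaves the count without a planning basis, and the second needs more patients, as shown above. Prevalence is the only outcome with a planning figure, so it is the natural choice.

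The cost is wording, and the polyp count gives up its primary status. Neither the sample size nor any study procedure changes.

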### Drug supply

Metformin will be purchased from Dainippon Sumitomo Parma Co., Ltd. The placebo (250 mg lactose) will be purchased from Kokando Co., Ltd, Toyama, Japan. All trial drugs will be packaged identically and identified only by number. Subjects will be instructed to take one tablet of the trial drug after breakfast every day, and to visit the hospital every 4 weeks for evaluation of the subjective symptoms and for receiving a new supply of medication. Compliance will be monitored by counting the empty drug packages returned by the patients at every visit to the outpatient clinic.

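### A Grade 3 or worse adverse event takes the patient out of the study, not only off study drug, so the 1-year outcome and later adverse events are lost

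*Protocol article*

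**What the plan says.** The rule stands in the protocol article under Outcome measurements, in the item on drug safety. The trigger is severity alone: "If Grade 3 or more severe adverse events appear, the follow-up doctor shall report it (them) to the coordinating office", and then "the case will be withdrawn from the study at that point". No relation to the trial drug is required, and what ends is the study, not the tablets.

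Three other statements decide what that means for the data.

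- **Primary outcome.** Outcome measurements: "The primary endpoint shall be the prevalence of colorectal polyps and number of polyps after 1-year's intervention". Its timing is given under Intervention: "At the end of 1 year of administration of metformin/placebo, colonoscopy will be performed to evaluate the polyp formation".
- **Safety data.** Outcome measurements: "adverse events will be monitored by the doctor at every follow-up visit to the outpatient clinic". Under Drug supply, patients are told "to visit the hospital every 4 weeks for evaluation of the subjective symptoms and for receiving a new supply of medication". Statistical analysis adds: "The safety, one of the secondary endpoints, will be similarly compared by the chi-square test".
- **Examination at 1 year.** Later in the same list of secondary outcomes: "All participants will receive physical examination and laboratory tests at the time of the 1-year endoscopic examination and polypectomy". No exception is made for withdrawn cases.

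**The concern.** Stopping a drug and leaving a trial are different events. A patient who stops the drug can still supply the outcome; a patient withdrawn from the study cannot. Here the two are merged for the patients with the most severe events.

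Two things are at stake. First, the primary comparison would lack patients who were removed after randomisation because of something that happened on treatment. If metformin alters how often such events occur, the losses differ between arms and the remaining groups are no longer the groups that were randomised. Second, safety is a stated aim, and the Discussion makes confirmed safety of chronic use in non-diabetic patients the condition for a longer trial. Observation would nevertheless stop in the patients who have just had a serious-grade event.

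This is a rule of conduct, so it matters before data collection. A later analysis plan can define populations and handle missing values, but it cannot recover colonoscopies and adverse events that sites were told not to collect.

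**Working it through.** **1. Following the text for one patient.** Suppose a Grade 3 event occurs in month 3.

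- The event is reported to the coordinating office, so it is captured.
- The patient leaves the study at that point and never completes a year of administration, which is the time point to which the outcome colonoscopy is tied. Nothing in the article provides a colonoscopy for such a patient.
- The 4-weekly visits at which symptoms are assessed are also the drug-supply visits. Nothing keeps a withdrawn patient attending them, so later adverse events go unrecorded.
- Yet the same section has all participants examined and tested at the 1-year endoscopy. Both statements cannot hold for this patient.

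**2. The plan's own sample size.** Inputs from Sample size estimation: rates 26/48 = 0.5417 and 15/48 = 0.3125, two-sided 5%, power 80%, 68 per group, 10% dropout, 75 recruited per group.

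Unpooled normal approximation: n = (1.960 + 0.842)² × [p₁(1 − p₁) + p₂(1 − p₂)] / (p₁ − p₂)² = 7.849 × (0.2483 + 0.2148) / 0.05252 = 69.2, so 70 per group. This is within 2 patients of the stated 68. The stated figure is taken as it stands. For dropout, 68 × 1.10 = 74.8, giving 75. The allowance is therefore 75 − 68 = 7 patients per arm, for all reasons together.

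**3. How far could losses move the primary test?** The document gives no rate of Grade 3 or worse events, so the number lost is an assumption and is varied. At the planned rates, 68 × 0.5417 = 36.8 (37) placebo and 68 × 0.3125 = 21.25 (21) metformin patients have polyps. Pearson chi-square without continuity correction; lost patients are added back with an assumed outcome:

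| Assumption about lost patients | Metformin | Placebo | P |
|---|---|---|---|
| None added back | 21/68 (30.9%) | 37/68 (54.4%) | 0.0055 |
| 2 metformin, both with polyps | 23/70 (32.9%) | 37/68 | 0.011 |
| 3 metformin, all with polyps | 24/71 (33.8%) | 37/68 | 0.014 |
| 7 metformin, at about the placebo rate (4 of 7) | 25/75 (33.3%) | 37/68 | 0.011 |
| 7 metformin, all with polyps | 28/75 (37.3%) | 37/68 | 0.041 |
| 7 metformin all with polyps, 7 placebo with none | 28/75 (37.3%) | 37/75 (49.3%) | 0.138 |

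The last two rows are extremes. They assign the whole dropout allowance to this one rule and assume the least favourable outcome for every lost patient.

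**4. Bias if there is no true effect.** Take prevalence 54.2% in both arms and losses of k out of 75 in the metformin arm only. With q the prevalence among those lost, observed prevalence = (75 × 0.5417 − k × q) / (75 − k).

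- k = 4: from −2.6 points (q = 1) to +3.1 points (q = 0).
- k = 7: from −4.7 to +5.6 points.

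**5. Power.** By the pooled formula, 75 per group with no losses gives 81.6%. If Grade 3 or worse events were the only losses, at 5% metformin and 2% placebo it is 80.2%; at 10% and 5% it is 78.5%. On top of the planned 10% dropout, power goes from 77.4% with no such events to 75.9% and 74.0% respectively. Over this assumed range the cost is about 1 to 3 points.

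**The case against.** The strongest reply is that the article condenses a fuller protocol, and that withdrawal may be shorthand for ending trial treatment. Nothing states outright that a withdrawn patient gets no colonoscopy, that later events go uncounted, or that the patient is left out of the analysis; the sentence about all participants even points the other way. That much is fair: what the authors intended is uncertain. But the sentence names the study, sites would apply it as written, and the contradiction has to be resolved on either reading.

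A reader might infer more than the document supports.

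- **That the losses are treatment-related.** The rule covers events of any cause in both arms, and the doctors applying it are blinded to allocation. Diarrhea is named as the most frequent metformin-related event, but nothing says that it reaches Grade 3. The article calls the low dose safe in the earlier study and links gastrointestinal effects to high doses. Differential loss is possible, not shown.
- **That the trial's conclusion would be overturned.** The extreme bounds do not show this. No Grade 3 or worse rate is given, and with 2 or 3 such losses the planned result stands.
- **That safety data on the worst events vanish.** The triggering event is reported, and a comparison of patients with events would keep it. Only later events in those patients are at risk.
- **That the plan adopts an analysis of tolerators only.** No analysis population is stated, and its definition, like the choice of sensitivity analyses, can properly sit in the analysis plan.

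The 10% dropout allowance does not answer the point: it replaces numbers, not comparability.

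**Conclusion.** The point holds in a limited form. As written, the rule removes patients with a Grade 3 or worse event from the study, which forfeits their 1-year outcome and any later adverse events, and it contradicts the 1-year examination of all participants. This rests on reading the sentence literally and on the absence of any provision in the article for continued follow-up of such patients.

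The numerical consequence is probably small: P moves from 0.0055 to between 0.011 and 0.014 for 2 or 3 metformin losses all with polyps, with about 1 to 3 points of power lost over the assumed event rates. The defect concerns mainly who is compared and which safety data exist. It should be fixed, but it does not by itself invalidate the trial.

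**What to change.** Reconcile the two statements under Outcome measurements by separating two decisions. Discontinuation of study drug after such an event stays under the existing clinical rule, on which no view is taken here. Withdrawal from the study becomes a separate event that this trigger no longer causes. Patients with such an event, if they consent, remain in adverse-event follow-up, are invited to the scheduled colonoscopy 1 year after randomisation, and are counted in their assigned arm. The Intervention section's timing, now tied to completed administration, needs the same adjustment so that it covers patients who stopped early.

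The cost is a small amendment, plus visits and a colonoscopy for what may be a handful of patients. The effect estimate may be slightly diluted because it will include patients off drug. The change is worth making before sites apply the rule, since data not collected cannot be recovered.
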